## Abstract

**Background:**

Various media are used to enhance public understanding about diseases. While mobile health apps are widely used, there is little proof for using such apps to raise awareness of skin diseases.

**Objective:**

We intend to develop an app, called DEDIKASI-app, to raise awareness of skin diseases, including leprosy. The study will explore baseline awareness, assess the app’s acceptance by community members and health care workers, and evaluate its effectiveness in enhancing awareness about skin diseases.

**Methods:**

The study will be conducted in four phases: (1) development of DEDIKASI-app, (2) questionnaire development for an awareness study, (3) acceptability testing, and (4) effect measurement of DEDIKASI-app. We will adopt design thinking methodology to develop the app, involving systematic reviews, expert consultations, focus group discussions, and validation of the questionnaire on skin disease awareness. We will recruit 50 members of the community for the awareness and acceptability study and 1 health care worker per community health center to assess their perception of the app. A pilot study will assess the acceptability of DEDIKASI-app among community members and health care workers based on various constructs, with responses categorized as positive, negative, or undecided. The validity and reliability of a newly developed questionnaire on skin disease awareness will be tested, with validity results analyzed qualitatively and reliability measured using Cronbach α. The effectiveness of DEDIKASI-app in improving community awareness will be evaluated through a randomized controlled trial, using total scores, means, and SDs for control and intervention groups. Statistical significance of awareness level changes will be determined by delta change (*P* value), with *P*<.01 considered significant.

**Results:**

This study received ethical approval from the Ethics Review Board of the Faculty of Public Health, Universitas Airlangga (160/EA/KEPK/2023) and was registered in the Indonesia Clinical Research Registry (INA-O8EX278). Funding for the field research was secured in the period of May 2022-December 2024 from NLR Indonesia and Erasmus University Medical Center. As of manuscript submission, phase 1 (app development) and phase 2 (questionnaire development) have been completed. Data collection for the randomized controlled trial has just finished and data analysis is ongoing, with publication of the study results expected in late 2025.

**Conclusions:**

Innovative approaches are required to enhance awareness in the community. This study will introduce new tools and insights to address the limited knowledge about detecting skin problems.

**Trial Registration:**

INA-CRR Indonesia Clinical Research Registry INA-O8EX278; https://tinyurl.com/ms3k5yvn

**International Registered Report Identifier (IRRID):**

DERR1-10.2196/64057

## Introduction

Skin diseases are common all over the world. They can range from non–life-threatening conditions such as acne, contact dermatitis, benign tumors, atopic dermatitis (eczema), and psoriasis to more serious conditions such as autoimmune diseases and skin cancers. A particularly important group of skin diseases, categorized as neglected tropical diseases (NTDs), afflict disadvantaged communities in low- and middle-income countries [1,2]. These include Buruli ulcers, cutaneous and postkala azar dermal leishmaniasis, lymphatic filariasis, onchocerciasis, mycetoma, yaws, chromoblastomycosis and other deep mycoses, scabies and other ectoparasites, and leprosy [2]. Many of these conditions can cause lasting physical and mental complications and are associated with stigma. Leprosy is a typical example of such an NTD, with nearly 200,000 new cases reported worldwide in 2021 [3].

Detection delay is an important factor associated with disabilities in leprosy [4]. The stigma associated with leprosy, often exacerbated by a lack of understanding, challenges early detection considerably [5,6]. Stigmatization leads people to hide their condition, and this avoidance behavior results in delayed diagnosis and treatment [7-10]. The combined lack of knowledge and stigma creates barriers for prompt implementation of case finding and adherence to treatment protocols, undermining the overall effectiveness of leprosy control [7,11-13]. A pivotal element of timely detection is fostering self-awareness among populations at risk. Increasing public awareness on the relevance of early detection holds the potential to shift attitudes and behaviors toward increased health-seeking behavior [14]. This holistic approach should also target dispelling myths and misconceptions tied to leprosy. Furthermore, reinforcing health care systems is crucial to ensure streamlined diagnostic and treatment processes, while guaranteeing respectful and sensitive care for affected individuals [15-17].

National programs use information, education, and communication media to improve the knowledge and awareness of the community about health conditions and diseases. Both printed and electronic media are used widely for showcasing innovative approaches used to disseminate health-related messages [18]. The surge in mobile phone use has allowed health care support through mobile health (mHealth), a subset of eHealth. mHealth involves the application of mobile computing and communication technologies in health care and public health, commonly realized through mobile applications [10,18]. In 2018, the World Health Organization introduced an eHealth guidance book advocating mobile apps to enhance health services and achieve universal health coverage [19]. Aligning with this initiative, the Indonesian Ministry of Communication and Information initiated the Smart Health Initiative to digitize health services in the country [20]. The distribution of apps, however, varies across disease conditions and intended goals. Moreover, there is currently no evidence supporting the use of an app for raising awareness about early leprosy detection [21].

The proposed study entails the creation of a 2-way integrated mobile app known as DEDIKASI-app (“dedication” in English and would be application-based early skin detection translated from the Indonesia abbreviation), catering to both users and health care workers (HCWs). The application aims to raise awareness about early skin detection, encompassing possible leprosy cases and other prevalent skin conditions. Because of the stigma toward leprosy in the community, this study extends its scope to include common skin diseases within the app.

The study aims are as follows: (1) to develop a mobile app (DEDIKASI-app) as an awareness-raising strategy in the community for early signs of common skin diseases, (2) to develop a skin diseases awareness questionnaire, (3) to provide insight into the acceptability of DEDIKASI-app to the community and HCWs, and (4) to assess its effectiveness in improving community awareness of common skin symptoms.

## Methods

### Overview

The study will be conducted in four phases: (1) development of the DEDIKASI-app mobile app, (2) development of a questionnaire to measure the level of awareness in the community of common skin diseases, (3) an awareness study and acceptability test of DEDIKASI-app, and (4) a randomized controlled trial of DEDIKASI-app. The phases of this study are outlined in Figure 1.

**Figure 1 figure1:**
[figure not shown]
Flowchart of the 4 phases of the study.

### Phase 1: Development of DEDIKASI-app

We will apply a comprehensive approach to create an effective and user-friendly platform for common skin disease detection and awareness promotion. The platform is called DEDIKASI-app, an acronym of deteksi dini kusta berbasis aplikasi*,* which translates to application-based early skin detection. DEDIKASI literally means “dedication,” portraying the dedication to achieve leprosy elimination by increasing awareness and early diagnosis using this DEDIKASI-app.

DEDIKASI-app is a 2-way platform aimed at the general community (DEDIKASI-P) and HCWs (DEDIKASI-HCW) within community health centers (CHCs, puskesmas in Indonesia). The front end of the platform is openly accessible to the public while the back end is only accessible to HCWs functioning on Android devices with or without internet connectivity. While the front end allows offline reading of information, active tasks, such as skin self-detection and uploading, require internet access. Similarly, the back end can function offline for reading, but internet connectivity is essential for notifications and responses.

DEDIKASI-P will include an animated anatomy feature and a detailed catalogue of skin symptoms to assist users in self-assessment by offering valuable information. After completing the self-assessment, HCWs can review the results through DEDIKASI-HCWs, enabling internet-based consultations or scheduling in-person appointments.

Before developing the app, we conducted a systematic literature review of studies on mHealth apps and interventions to explore strategies and tools for promoting mHealth interventions aimed at promoting early detection and increasing awareness of chronic diseases [22]. This review helped identify various approaches to enhance early detection and awareness while also incorporating strategies to maintain user engagement. Additionally, expert consultations were carried out to design a user-friendly interface accessible to all community members, regardless of their educational background.

The mobile apps will be developed by identifying suitable design architecture and an interface aligned with its intended purpose. This step will entail outlining the overall requirements for app development, with content generated in the Indonesian language. DEDIKASI-app will be entirely self-developed, including its visual design and animations, ensuring that no copyrighted materials from other apps or owners are used in its development. Design thinking methodology [23], a human-centered approach, will be adopted to delineate the standardized process used in crafting the app. This methodology focuses on user needs and considers various stakeholders’ perspectives, involving HCWs closely in the development process [23].

We emphasize that DEDIKASI-app is not intended to replace the role of health care professionals in diagnosing common skin diseases. Instead, the app will serve as an interactive and communicative tool for raising awareness. The app aim to stimulate early common skin disease detection, particularly of leprosy, preventing severe physical and mental outcomes and stigma. Additionally, the users will be encouraged to seek help from HCWs by using DEDIKASI-app when they identify potential skin symptoms. Given the social isolation and stigmatization faced by individuals with leprosy, the app’s internet-based services offer empowerment and privacy, allowing for self-testing and reducing stigma-related fears [24-26]. However, the role of health care professionals remains crucial in case finding, diagnosis, and management of leprosy.

Based on prior studies, strategies will be selected to attract users, such as attractive animations, tailored messages, and rewards (eg, receiving a shopping voucher). Visual appeal, ease of use, social support, and trust are factors that encourage health app usage [27-29]. The app will feature an anatomy animation and a comprehensive list of skin symptoms aimed to aid the users in self-assessment by providing helpful information.

Although the main objective of DEDIKASI- app is to increase awareness about leprosy, given the stigma about leprosy, we decided to expand the context of the app to common skin diseases.

DEDIKASI-app will be developed by a recognized digital health agency in Indonesia called Databiota. The Databiota team will use Android Studio to develop the app’s software, with initial user evaluation during app prototyping. A navigating map (site map and screen flow diagram) will be applied for modeling graphs to describe the interface map. Version control and update tracking will be reported once the app is finalized and the trial begins.

App development will be funded by NLR Indonesia. The app will be owned by the research group on Tropical Diseases, Infectious Diseases and Herb in the Faculty of Public Health Universitas Airlangga in Surabaya, Indonesia.

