### Phase 2: Development of a Questionnaire for Measuring Awareness of Common Skin Diseases in the Community

The literature review showed the absence of specific instruments for measuring the level of awareness in the general community of early symptoms of common skin diseases. Thus, in this second phase of the study, we aim to develop a questionnaire for measuring awareness in the general community, which will assess common skin disease knowledge, common skin disease prevention, and the intention to seek health services.

The questionnaire will be developed in 2 steps. The first step involves conducting a literature review, consultation with professional experts, and focus group discussions with persons with and without knowledge or expertise in leprosy. Questions will initially be developed in English based on expert judgement and checks by English language experts. Because the study population is Indonesian, the second step will involve translating the questionnaire into the Indonesian language.

The validity and reliability study for the developed questionnaire will be conducted in the subdistrict of Batumarmar, Pamekasan District, East Java Province, ensuring the questionnaire accurately measures the awareness of the community regarding skin diseases and produces consistent results over time and different respondents. The Batumarmar area was chosen because of its variety of geographic and community characteristics, which include rice fields, mountains, and residential areas in both urban and rural settings. Study participants will include experts in leprosy and behavioral sciences (the study supervisor), local key informants, and members of the general community.

The eligibility criteria for the validity and reliability study are as follows: (1) residents living in Batumarmar subdistrict and Pamekasan District; (2) individuals aged 18-65 years; (3) individuals willing to participate and provide informed consent; and (4) individuals able to understand and communicate in Indonesian and Madurese languages. Aside from the results of the validity and reliability test, data on demographical characteristics, such as gender, age, educational level, and occupation, will be included for analysis.

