### Phase 4: Randomized Controlled Trial of the Effectiveness of DEDIKASI-App to Increase Early Detection of Skin Diseases Including Leprosy

The fourth phase is an randomized controlled trial aimed to assess the effectiveness of DEDIKASI-app as a strategy to increase awareness and early detection of leprosy and other common skin diseases.

The sample size will be calculated using the following formula for hypothesis testing for 2 population means (2-sided test) [33]:

The following values will be used: level of significance (α)=5%; power of the test (1-β)=90%; population SD (σ)=5; and population variance (σ^2^)=25. The population mean (µ_1_) will be obtained after the awareness study in the second phase; as there was no previous study available, µ_2_ represents the anticipated population mean of the intervention group. Sample size will be calculated afterward; however, we will expect to obtain 600 participants.

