The study population is the general community located in 21 CHCs of Pamekasan District. The participating CHCs have already been randomly allocated to either the intervention or control group using a computer-generated sequence by an independent statistician. The intervention group comprises Tlanakan, Bandaran, Pademawu, Sopaah, Galis, Larangan Bedung Kadur, Batumarmar, Teja, and Kowel, and the control group comprises Larangan, Talang, Proppo, Panaguan, Palengaan, Pakong, Waru, Tampojung Pregi, Pasean, Pengantenan, and Bulangan Haji. Allocation concealment was ensured by using sequentially numbered, sealed, opaque envelopes, opened only after enrolment of each cluster. Research assistants will enroll participants through door-to-door recruitment*.* To reduce information contamination, we will ensure geographical separation of intervention and control CHCs where feasible. Pamekasan District, located on Madura Island in East Java Province, covers an area of approximately 792 square kilometers, with a population density of around 850 people per square kilometer. The district is divided into 13 subdistricts, with substantial distances between them; for example, the distance between Batumarmar (a northern subdistrict) and Proppo (a central subdistrict) is approximately 25 kilometers, often requiring over an hour’s travel due to rural road conditions. Given this geographic spread and limited daily intervillage interactions, the risk of information spillover between intervention and control clusters is considered minimal. Baseline and postintervention surveys will be conducted within a short period of a fixed 4-week window across all clusters to minimize variation due to external influences such as health campaigns or seasonal trends. Data collectors will follow the arranged schedule based on the study procedure. For eligibility to participate in the study, participants must be a resident of Pamekasan District, especially in the working area of the 21 CHCs; aged 18-65 years; willing to participate in the study and provide informed consent; and an android or smartphone user. The final criterion might not apply to the control group.

Data regarding the effectiveness of DEDIKASI-app as a strategy to increase awareness and early detection of leprosy and other common skin diseases will be collected using the validated questionnaire that will be developed in phase 2.

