### Statistical Analysis

Results of validity and reliability testing of the community awareness questionnaire developed in phase 2 will be analyzed using both descriptive and analytical statistics. Demographic data will be analyzed descriptively, while the validation and reliability of the questionnaire will be assessed statistically using Pearson correlation and Cronbach α, respectively. Content and face validity will be qualitatively used to avoid question item ambiguity, ensure clarity and relevancy, and ensure that the questions are not judgmental, intrusive, or distressing to target participants [34]. The questionnaire will be administered through an interview setting, with all selected respondents interviewed at 2 points: a preintervention interview and a postintervention interview conducted approximately 4 weeks later (during the intervention study in phase 4).

During the third phase, the questionnaire developed in phase 2 will be used to collect the data on awareness in the general community. All responses to the questions will be given numerical scores based on correct or positive answers. The total score will be calculated, while the mean range will be used to illustrate the distribution and variation of scores. To measure the impact of the intervention, the change in scores (delta change) between preintervention and postintervention assessments will be calculated for each group. The Wilcoxon signed-rank test will be used to compare paired preintervention and postintervention scores within each group. A *P* value of <.01 will be considered statistically significant, indicating improvements in respondents’ knowledge, prevention practices, and health-seeking behavior.

The acceptability test for DEDIKASI-app will be conducted during the third phase, using a survey based on the TAM. A Likert scale will be used as a scoring system. The results from both community members and HCWs will be descriptively analyzed and presented using a frequency table.

Data from the randomized controlled trial in the fourth phase will be analyzed using SPSS version 21 (IBM Corporation). We will conduct a descriptive analysis by calculating the either the mean or median values of the awareness scores and the count of reported common skin disease cases through DEDIKASI-app. The choice between mean or median will depend on the distribution of the scores. We will also use a box plot diagram to visually compare the measurements between the 2 groups.

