### Conclusion

This study is expected to contribute to new understandings on how communities recognize and perceive skin symptoms, with special reference to early-stage leprosy. It will also offer perspectives on how well DEDIKASI-app is received and how effective it is in enhancing awareness among both the community and health care professionals with regard to identifying leprosy and other common skin problems.

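### A total score on common skin diseases cannot by itself show that leprosy awareness rose, nor that knowledge, prevention and care seeking all improved

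*Protocol article*

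**What the plan says.** All references are to the protocol article.

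- **Purpose of the app** (Phase 1): the main purpose of the app "app is to increase awareness about leprosy, given the stigma about leprosy, we decided to expand the context of the app" to common skin diseases.
- **Study aim 4** (end of the Introduction): "to assess its effectiveness in improving community awareness of common skin symptoms". Leprosy is not named.
- **Aim of the trial** (Phase 4): to assess the app "as a strategy to increase awareness and early detection of leprosy and other common skin diseases". The same section says that data on this effectiveness "will be collected using the validated questionnaire that will be developed in phase 2".
- **Content of the questionnaire** (Phase 2): an instrument "which will assess common skin disease knowledge, common skin disease prevention, and the intention to seek health services".
- **Scoring** (Statistical Analysis): "The total score will be calculated, while the mean range will be used to illustrate the distribution and variation of scores". The Abstract ties total scores to the randomized comparison.
- **Reading of a significant result** (Statistical Analysis): a P value below .01 is taken as "indicating improvements in respondents’ knowledge, prevention practices, and health-seeking behavior".
- **Expected conclusions** (Conclusion): new understanding of how communities perceive skin symptoms, "with special reference to early-stage leprosy". The next sentence expects evidence on how far the app improves awareness for identifying leprosy and other skin problems.

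**The concern.** The trial's aim and its expected conclusions name leprosy, but the awareness outcome as fixed is one sum over all answers. A sum shows that something in the questionnaire moved, not which part. If the gain came from items on other conditions, the total could be significant while answers about leprosy stayed where they were.

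The same weakness affects the three domains. A significant change in the total is compatible with improvement in one domain and none in the other two, yet the article says in advance that it indicates improvement in all three. It also names the third domain as behavior, although the questionnaire is described as measuring intention to seek care.

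At stake is what the results paper can claim. Leprosy is the reason the app was built, and a claim that it raises leprosy awareness or changes care seeking would carry weight with health programs.

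**Working it through.** **1. Claim against measure**

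| Place | Target or measure | Leprosy named? |
|---|---|---|
| Introduction, aim 4 | Awareness of common skin symptoms | No |
| Phase 4, aim | Awareness and early detection, leprosy and other skin diseases | Yes |
| Phase 2, questionnaire | Knowledge, prevention, intention to seek care | Not as a domain |
| Abstract; Statistical Analysis, score | One total | No |
| Statistical Analysis, between-arm test | t test or Mann-Whitney test | No |
| Statistical Analysis, other measure | Count of skin disease cases reported through the app, descriptive | No |
| Strengths and Limitations | Monitoring of contacts with health centers | No |
| Conclusion | Effect on awareness for identifying leprosy and other skin problems | Yes |

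The two rows that claim something about leprosy rest on a measure that does not separate it. The case count and the monitored contacts are not measures of leprosy awareness.

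**2. Three domains from one total**

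Write the total as T = K + P + I (knowledge, prevention, intention). The mean change in T is the sum of the three mean changes. A positive sum does not imply that each term is positive. The sentence in question follows the within-group Wilcoxon test, so it concerns pre-post change within an arm, but the algebra is the same for a difference between arms.

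**3. Size, as an illustration**

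Inputs from the Phase 4 sample size paragraph: SD 5, two-sided alpha 5%, power 90%, 600 participants expected. The article gives neither group mean, so 600 cannot be reproduced; it can only be inverted. Assumptions: equal split (300 per arm), normal approximation, clustering ignored.

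- Standard error of the difference: 5 × √(2/300) = 0.408 points.
- Difference that 600 would detect: (1.960 + 1.282) × 0.408 = 1.32 points, or 0.26 SD.
- Smallest significant difference at P<.05: 1.960 × 0.408 = 0.80 points.
- Smallest significant difference at P<.01: 2.576 × 0.408 = 1.05 points.

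Both thresholds are shown because the article uses .01 for the change in scores and .05 for the between-arm comparison.

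Suppose the leprosy items do not change at all and the other items raise the total. The probability of a significant total at .05 is then:

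| Gain on other items (points) | Probability |
|---|---|
| 1.0 | 0.69 |
| 1.32 | 0.90 |
| 1.5 | 0.96 |
| 2.0 | 1.00 |

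At an assumed one point per item, 0.80 points corresponds to four non-leprosy items each answered correctly by 20 percentage points more participants (4 × 0.20). For 1.05 points, five items at 21 percentage points would do (5 × 0.21). No single one-point item could reach 1.05. Allowing for the allocation by health center would raise both thresholds, but the argument does not depend on their exact value.

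**The case against.** **The objective.** A reader might infer that the trial leaves its own main objective unanswered. The document does not support that. The main objective in Phase 1 is that of the app, and numbered aim 4 concerns common skin symptoms, which a total skin-awareness score does address. This stands. It leaves untouched the Phase 4 aim and the Conclusion, which do extend the claim to leprosy.

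**The content.** A reader might also infer that the questionnaire leaves leprosy out. That is not supported either. The article uses common skin disease as a term that includes leprosy, people with leprosy expertise helped to develop the questions, and the items are not shown. Some may well concern leprosy. Even so, a sum that includes them does not say whether they moved.

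**Silence.** Item lists and sub-scores are often left to a full protocol or analysis plan, and their absence from an article is no fault. This also stands. The point rests on what the article states: the leprosy aim, the total as the score, and an explicit three-domain reading of a significant change.

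**The quoted wording.** The scoring sentence sits in a paragraph that opens with phase 3. However, the Abstract applies total scores to the trial, and the paired pre-post interviews belong to phase 4. The early-stage leprosy phrase describes how communities perceive symptoms, so the effectiveness claim rests on the sentence after it.

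**Deliberate breadth.** Not singling out leprosy, because of stigma, is a reasoned choice and is not questioned here. Scoring items separately at analysis changes nothing that participants see.

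**Conclusion.** The point holds in a limited form. The total answers study aim 4. It cannot by itself support the leprosy part of the Phase 4 aim or of the Conclusion, and a significant pre-post change in it cannot show that three domains improved. The word behavior goes beyond the intention that the questionnaire is said to measure.

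The logic needs no sample size figure. The illustration (0.80 points at P<.05, 1.05 at P<.01) assumes 300 per arm, SD 5 and no clustering, and it shows only that a modest gain confined to other items would be enough. How likely such a pattern is cannot be judged without the items. The article does not say that a significant total will be reported as success on leprosy; it leaves that reading open. The change is worth making because it costs little and prevents an unsupported conclusion.

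**What to change.** 1. Keep the total score as the overall awareness outcome.
2. Compare the three domain scores between arms and report them separately.
3. Delete the statement that a significant change indicates improvement in all three domains, and refer to intention to seek health services instead of behavior.
4. If the questionnaire has leprosy items, define a leprosy sub-score before the arms are compared and report it as a secondary outcome. Data collection has ended and analysis is under way (Current Progress), so if the comparison has already been made, label the sub-score post hoc.
5. If it has no leprosy items, limit the claims in Phase 4, Anticipated Findings and the Conclusion to common skin diseases.

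**Cost.** Analysis and wording only; no new data are needed. The downsides are additional secondary comparisons, in a study that already says it is not powered to control for multiplicity, and lower precision for short sub-scores. As an illustration of the second, suppose the leprosy items carried a quarter of the variance (SD 5 × √0.25 = 2.5) and a quarter of a 1.32-point gain (0.33 points). Power at 300 per arm and two-sided 5% would be about 0.37, again ignoring clustering. A non-significant sub-score should therefore be read from its confidence interval and not as evidence of no effect.
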